### Data collection

Following the provision of written informed consent by the patients, baseline data will be collected. To standardize the procedural timeline and assess the impact of the interventions on workflow, the following time points will be recorded for all patients: the time of entering the operating room (T1), the time of completion of the nerve block or local anesthesia infiltration (T2), the time of surgical skin incision (T3), and the time of leaving the operating room (T4). The ‘anesthesia preparation time’ will be defined as the interval from entering the operating room (T1) to the completion of anesthesia intervention (T2). The ‘total operating-room occupancy time’ will be defined as the interval from entering (T1) to leaving (T4) the operating room. The ‘block-to-incision’ interval (T2 to T3) will also be calculated. The anesthesiologist responsible for the patient’s perioperative management, who is blinded to group assignment, will assess and record the patient’s VAS pain score at three specific timepoints: (1) during trocar insertion into the pedicle, (2) during polymethylmethacrylate bone cement injection, and (3) at the end of the procedure before transferring the patient out of the operating room. The intraoperative incidence of moderate-to-severe pain will be recorded. Postoperatively, the highest intraoperative pain score, patient satisfaction with intraoperative analgesia, and surgeon satisfaction will be obtained. The incidence of rescue analgesia within the first 24 h post-surgery, as well as the time to first mobilization, will be collected by an independent researcher. The incidence of adverse events will be recorded from the initiation of the intervention until patient discharge.

All data will be initially recorded on paper-based CRF. These data will then be entered into an Excel database, with verification performed by two independent individuals. Although an independent data monitoring committee was not established for this single-center trial, data accuracy and protocol adherence will be safeguarded through internal quality control processes under the supervision of the principal investigator and the institutional ethics committee.

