### Measures

#### Primary outcomes

The incidence of moderate-to-severe pain during the operation. This is defined as the proportion of patients reporting a VAS score > 3 at any of the predefined intraoperative timepoints (trocar insertion, cement injection, or end of procedure). Pain will be assessed using a VAS score (0–10), where a higher score indicates more severe pain.

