#### Data analysis

Statistical analysis will be performed using SPSS 27.0. The Shapiro-Wilk test will be used to assess normality. Normally distributed quantitative variables will be expressed as mean ± standard deviation, and compared between two groups using an unpaired *t*-test. Non-normally distributed quantitative variables will be expressed as median (interquartile range), and compared between two groups using the Mann-Whitney *U* test. Categorical variables will be expressed as number (percentage), and compared using the chi-square test or Fisher’s exact test. A *p*-value of less than 0.05 will be considered statistically significant.

All analyses will be conducted on an intention-to-treat basis. Any missing data will be handled based on the pattern and amount of missingness. For the primary outcome (incidence of moderate-to-severe pain), a missing value will be considered a treatment failure (*i.e*., included in the numerator for the incidence calculation) to provide a conservative estimate of the intervention’s effect. For secondary continuous outcomes (*e.g*., VAS scores), if data are missing at random and the proportion is small (<5%), complete-case analysis will be employed. If the proportion is larger, multiple imputation methods will be considered.

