#### Sample size

According to our center’s data, the incidence of moderate-to-severe pain during lumbar PVP under local anesthesia is 70%. Assuming that ESPB can reduce the incidence of moderate-to-severe pain by 50% (*i.e*., to 35%) (Sharma et al., 2024), with α = 0.05, 1 − β = 0.8, and performing a two-sided test, the sample size was calculated to be 62 cases (31 cases per group) using PASS 2023 software. Assuming a dropout rate of 5%, the final number of cases to be included is 66 (33 cases per group).

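### The comparisons of the primary outcome and of maximum intraoperative VAS use no baseline pain covariate; adjusting for pre-procedure pain is a cheap gain in precision, not the repair of an error.

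*Protocol article*

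**What the plan says.** - **Baseline (Protocol article, Data collection).** "Following the provision of written informed consent by the patients, baseline data will be collected". The items are not listed. The same section then names three VAS assessments: at trocar insertion, at cement injection and at the close of the procedure. All three come after the intervention.
- **Primary outcome (Primary outcomes).** A patient counts as an event with a "VAS score > 3 at any of the predefined intraoperative timepoints". This is an absolute threshold, not a change from a starting value.
- **Analysis (Data analysis).** "Categorical variables will be expressed as number (percentage), and compared using the chi-square test", with Fisher's exact test as the alternative. Continuous outcomes, which include maximum intraoperative VAS, go to an unpaired t-test or a Mann-Whitney test according to normality. No covariate and no adjusted model is named.
- **Sample size (Sample size).** The assumed rates are 70% under local anesthesia and 35% under ESPB, at a two-sided α of 0.05 and 80% power. On these inputs "the sample size was calculated to be 62 cases (31 cases per group) using PASS 2023 software". A 5% dropout allowance brings this to 66, or 33 per arm.
- **Population (Participants).** Users of preoperative analgesics and patients with chronic pain are excluded. No limit is set on current acute pain. Under Randomization, allocation is 1:1 and no stratification is described.

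**The concern.** The Introduction says vertebroplasty treats compression fractures and vertebral tumors, so some patients may already be in pain when they enter the operating room. Pain present beforehand may raise the VAS reported during the procedure, and the primary outcome applies a fixed cut-off to that VAS. If the two are correlated, an analysis that ignores the starting level leaves explainable variation in the error term. With 33 patients per arm and no stratification described, a chance difference in starting pain would also move the observed effect in one direction or the other.

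At stake are the precision of the estimate and how easily it can be read if the arms turn out to differ at baseline. An adjustment chosen only after such a difference is seen would look post hoc, so the decision belongs in the plan.

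**Working it through.** **1. The plan's own figure.** Inputs from Sample size: p₁ = 0.70, p₂ = 0.35, two-sided α = 0.05, power 0.80. Pooled-variance formula without continuity correction, with mean rate 0.525:

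n = [1.960·√(2·0.525·0.475) + 0.842·√(0.70·0.30 + 0.35·0.65)]² / 0.35² = [1.384 + 0.557]² / 0.1225 ≈ 30.8, so 31 per arm and 62 in total.

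Dropout: 62 / 0.95 = 65.3, so 66. The stated size reproduces. At 33 per arm, exact enumeration of the uncorrected chi-square test gives power of 85.6%.

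**2. Chance imbalance in baseline pain.** The standard error of the standardised difference between arms is √(2/33) = 0.246, so the 95% range is ±1.96 · 0.246 = ±0.48 SD. A gap above 0.25 SD has probability about 31%; above 0.5 SD, about 4%.

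Only the fraction r of a gap carries over to the intraoperative score. On a latent-normal scale the density at the threshold is 0.348 (rate 70%) and 0.370 (rate 35%), mean 0.359. A gap at the 0.48 SD limit therefore shifts the risk difference by about 0.48 · r · 0.359: about 5 points at r = 0.3 and 9 points at r = 0.5, against a planned difference of 35.

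**3. Maximum VAS.** ANCOVA multiplies the error variance by 1 - r². The effect is set so that the unadjusted test has 80% power at 33 per arm, a standardised difference of 0.246 · (1.960 + 0.842) = 0.69:

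| r (assumed) | variance removed | adjusted power |
|---|---|---|
| 0.2 | 4% | 82% |
| 0.3 | 9% | 84% |
| 0.4 | 16% | 86% |
| 0.5 | 25% | 90% |
| 0.6 | 36% | 94% |

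The gain survives a bounded, rounded 0-10 score. There, Mann-Whitney against ANCOVA gave power of about 77% against 82% at r = 0.3 and 77% against 88% at r = 0.5, with no loss at r = 0.

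**4. Binary primary outcome.** Simulation with a latent-normal pain score, 33 per arm, 70% against 35%, 20,000 trials per setting. The uncorrected chi-square test is set against a baseline-adjusted logistic likelihood-ratio test. The last column compares the standardised risk difference with the raw one:

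| r (assumed) | chi-square | adjusted logistic | change in variance of risk difference |
|---|---|---|---|
| 0 | 86% | 84% | +2% |
| 0.3 | 85% | 85% | -4% |
| 0.4 | 86% | 87% | -8% |
| 0.5 | 86% | 89% | -13% |
| 0.6 | 86% | 92% | -20% |

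Chi-square power does not depend on r; the differences in that column are simulation error around 85.6%. Rounded, the change in power is about -2, 0, +1, +3 and +5 to 6 points. With both arms at 70%, type I error was 5.3% to 5.5% unadjusted and 5.5% to 5.7% adjusted, so neither test has a material validity problem.

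**The case against.** The strongest reply is that nothing here is wrong. The unadjusted chi-square is valid under randomization, chance imbalance is already covered by its error rate, it matches the method used to size the trial, and a supportive adjusted model could sit in an analysis plan that is not shown. All of that stands, and it is why this is a precision point.

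Three further objections also stand in part.

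- **Recording.** A reader might infer that no pre-procedure pain score is collected. The article does not support that: its baseline data are not itemised, and the full protocol is a supplement not shown. What is sure is that none is named and that the stated tests would not use one.
- **Size of the gain.** A reader might infer that one baseline VAS would remove the noise and the imbalance. Recording a score changes nothing by itself, and adjustment removes only the share that baseline pain explains. For the primary outcome that is worth nothing in power at r = 0.3, and adjustment costs about 2 points at r = 0.
- **Mechanism.** The Introduction attributes intraoperative pain to cement injection, vertebral expansion and needle insertion, which is evoked pain. Excluding analgesic users and patients with chronic pain may also narrow the spread of baseline scores. Both could make r small. Neither rules out acute fracture pain, and the article gives no correlation either way.

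**Conclusion.** The point holds as an inexpensive improvement in precision. As written, neither the primary comparison nor that of maximum VAS draws on baseline pain. The case is firmer for maximum VAS: 9% of variance removed at r = 0.3, 25% at r = 0.5, and no material loss if r is 0. For the primary outcome it is conditional: about 2 points of power lost at r = 0, none gained at r = 0.3, about 3 gained at r = 0.5 and 5 to 6 at r = 0.6.

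These sizes rest on an assumed r between 0 and 0.6, a latent-normal pain score, and the article's own rates of 70% and 35%. They do not support reading the planned tests as biased or the sample size as wrong: the type I error is held and the calculation reproduces.

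**What to change.** 1. State whether a resting VAS on the same 0-10 scale is among the baseline data and is taken before the envelope is opened. If it is not, add it.
2. For maximum intraoperative VAS, prespecify ANCOVA with baseline VAS as the single covariate.
3. For the primary outcome, prespecify a logistic model adjusted for baseline VAS, giving a standardised risk difference with 95% CI, reported alongside the unadjusted chi-square. Say in advance which of the two carries the primary conclusion.

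Cost: at most one item on the case report form and a sentence or two under Data analysis, with no additional patients. The statistical downside is up to about 2 points of power on the adjusted primary test if baseline pain proves unrelated to intraoperative pain. If the score is already collected, only the analysis text changes.

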### Interventions

LA group: Patients will be placed in a prone position. The surgeon will disinfect, drape, and after localization, will use 1% lidocaine for local infiltration anesthesia.

ESPB group: Patients will be placed in a lateral decubitus position. This position is standard for performing a bilateral lumbar ESPB as it provides optimal ergonomics for the operator, facilitates ultrasound probe placement, and allows for stable needle access to the transverse processes on both sides. An independent nerve block specialist (with over 3 years of experience in ultrasound-guided nerve blocks) will perform a bilateral ESPB in the operating room. The block will be performed at the vertebral level corresponding to the planned surgical level (*i.e*., the level of the vertebral fracture). A curvilinear probe (2–5 Hz) will be selected, and a parasagittal approach (approximately 3 cm lateral to the posterior midline) will be used for localization. The transverse process of the target vertebral level will be located, and a 24 G needle will be inserted in-plane to the surface of the transverse process. After negative aspiration for blood and cerebrospinal fluid, 3 mL of normal saline will be injected to separate the erector spinae muscle from the transverse process to confirm correct placement. A total of 20 mL of 0.25% ropivacaine will be administered at this level to achieve cranio-caudal spread of local anesthetic within the fascial plane. The same procedure will be performed on the contralateral side.

Concurrently, during the performance of the nerve block, the surgical team will use this time to prepare the sterile instruments and mix the polymethylmethacrylate bone cement. Upon completion of the bilateral blocks, the patient will be promptly assisted into the prone position. The surgical field will then be disinfected and draped in the standard fashion. A standardized minimum block-to-incision interval of 20 min will be maintained between the completion of the block and the surgical skin incision to allow for adequate sensory blockade onset.

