#### Secondary outcomes

Anesthesia preparation time: Defined as the time from patient entry into the operating room to the completion of the assigned anesthesia procedure (ESPB or local infiltration).

Total operating-room occupancy time: Defined as the time from patient entry into to exit from the operating room.

Maximum intraoperative pain score: This will be evaluated using the VAS, ranging from 0 to 10, where higher scores indicated greater pain intensity.

Intraoperative patient satisfaction with analgesia: This will be assessed *via* the VAS, ranging from 0 to 10, with higher scores reflecting greater satisfaction with the pain management provided.

Surgeon satisfaction with analgesia: Surgeon satisfaction will be evaluated using the VAS, ranging from 0 to 10, where higher scores represented greater satisfaction with the analgesia.

Incidence of rescue analgesia within the first 24 h postoperatively: This will be analyzed as a binary outcome (yes/no), representing the proportion of patients requiring any supplemental pain medication within the specified timeframe.

Total perioperative opioid consumption: The total consumption of all rescue opioids administered from the start of the procedure until 24 h postoperatively will be recorded. Intraoperative sufentanil and postoperative tramadol doses will be converted to intravenous morphine milligram equivalents (MME).

Time to first mobilization: This will be defined as the time elapsed until the patient is able to get out of bed for the first time following the procedure.

Incidence of adverse events: Adverse events, including local anesthetic toxicity, hemorrhage, nerve injury or infection, and pneumothorax, will be recorded.

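### Anesthesia preparation time (T1–T2) covers different steps in each arm, so its comparison understates ESPB's extra time to incision

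*Protocol article*

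**What the plan says.** Data collection in the Protocol article records four times for every patient: room entry (T1), "the time of completion of the nerve block or local anesthesia infiltration (T2"), skin incision (T3) and room exit (T4). The stated purpose is to standardize the timeline and to assess how the interventions affect workflow.

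Anesthesia preparation time is the "interval from entering the operating room (T1) to the completion of anesthesia intervention (T2"). Secondary outcomes repeats the definition for both arms: "Defined as the time from patient entry into the operating room to the completion of the assigned anesthesia procedure (ESPB or local infiltration"). The Abstract also names it. Under Data analysis, quantitative variables are compared between groups by t-test or Mann-Whitney test.

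Interventions fixes the order of steps:

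- LA arm: "LA group: Patients will be placed in a prone position". Then "The surgeon will disinfect, drape, and after localization, will use 1% lidocaine for local infiltration anesthesia".
- ESPB arm: the patient lies on the side, the transverse process is found by ultrasound, and both sides are blocked. "Upon completion of the bilateral blocks, the patient will be promptly assisted into the prone position". Disinfection and draping follow. "A standardized minimum block-to-incision interval of 20 min will be maintained", counted from the end of the block to skin incision.

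Two other intervals are planned. Total operating-room occupancy (T1–T4) is a listed secondary outcome. T2–T3 will be calculated but is not in the secondary outcome list.

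**The concern.** One label is applied to two different bundles of work. In the LA arm the clock stops after the patient has been prepared for surgery, because infiltration is done on a draped field. In the ESPB arm it stops before that preparation begins, and also before the onset interval that the protocol requires for the block.

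A formal comparison of T1–T2 is therefore not a comparison of how long each strategy takes to make a patient ready for incision. The Discussion anticipates smoother workflow if ESPB proves beneficial. A null or favourable T1–T2 result could be cited in support of that while ESPB patients reach incision later.

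**Working it through.** The article gives no figure for preparation time, so there is no stated number to reproduce. The only duration it supplies is the 20-min minimum. The check has three steps.

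**1. Place each step before or after T2** (Interventions, with T2 from Data collection).

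| Step | LA | ESPB |
|---|---|---|
| Lateral positioning | not applicable | before T2 |
| Ultrasound localization and bilateral block | not applicable | before T2 |
| Prone positioning | before T2 | after T2 |
| Disinfection and draping | before T2 | after T2 |
| Surgical localization | before T2 | not stated |
| Lidocaine infiltration | before T2, ends at T2 | not applicable |
| Mandated interval to incision | none stated | starts at T2, at least 20 min |

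In the ESPB arm, turning, disinfection and draping take place inside the 20 min. They do not add to it.

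**2. Size of the understatement.** Let D12 be the ESPB-minus-LA difference in T1–T2, and D13 the same difference in T1–T3. Since T1–T3 = T1–T2 + T2–T3 in each arm,

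D13 − D12 = (ESPB T2–T3) − (LA T2–T3) ≥ 20 − x,

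where x is the LA T2–T3 interval. The article does not give x, so a range is assumed:

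| Assumed x (min) | D13 exceeds D12 by at least (min) |
|---|---|
| 0 | 20 |
| 2 | 18 |
| 5 | 15 |
| 10 | 10 |

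The direction is guaranteed for any x below 20 min.

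**3. Can the sign of D12 be predicted?** This needs step durations that the article does not give. The scenarios below are assumptions in minutes: P prone positioning, D draping, L surgical localization, I infiltration, B lateral positioning plus block, and x as above. Time common to both arms is left out. Surgical localization in the ESPB arm is assumed to come after the block.

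- LA: T1–T2 = P + D + L + I, and T1–T3 = that sum + x.
- ESPB: T1–T2 = B, and T1–T3 = B + max(20, P + D + L).

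| P, D, L, I, B, x | LA T1–T2 | ESPB T1–T2 | D12 | LA T1–T3 | ESPB T1–T3 | D13 |
|---|---|---|---|---|---|---|
| 3, 5, 5, 3, 10, 1 | 16 | 10 | −6 | 17 | 30 | +13 |
| 5, 10, 5, 5, 15, 2 | 25 | 15 | −10 | 27 | 35 | +8 |
| 5, 10, 10, 5, 20, 5 | 30 | 20 | −10 | 35 | 45 | +10 |
| 3, 5, 3, 2, 20, 1 | 13 | 20 | +7 | 14 | 40 | +26 |

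D12 runs from −10 to +7 and D13 from +8 to +26. The sign reverses in three of the four scenarios and stays the same in the fourth. A reversal is possible but does not follow from the article.

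**The case against.** The strongest reply is that the omitted time is measured elsewhere. T1–T4 is a named secondary outcome and contains every step in question, and T2–T3 will be calculated. This limits the harm but does not remove it. T1–T4 also carries the operating time and its variability, so it does not isolate preparation. T2–T3 is not a listed outcome, and nothing says that it will be read together with T1–T2.

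It can also be said that time to completion of the anesthetic procedure is a legitimate quantity, explicitly and consistently defined. That stands for the definition as such. But the clock starts at room entry, so in the LA arm the interval also counts surgical preparation, and the stated purpose is workflow impact.

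A third reply is that T1–T3 contains a protocol minimum in one arm only, so its comparison is partly fixed by design. This is true and should be stated in the report. It is still time that the patient spends before incision under that strategy.

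A reader might infer three stronger things that the article does not support:

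- That the comparison will make ESPB look faster. Only the understatement of its extra time follows; the sign depends on durations not given.
- That the ESPB interval leaves out positioning and localization altogether. It includes lateral positioning and ultrasound localization, and the article does not say when surgical localization takes place in that arm.
- That turning and draping are lost on top of 20 min. They run within it.

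**Conclusion.** The point holds for the construction of this outcome. T1–T2 covers different steps by arm, and its between-group contrast understates ESPB's extra time to incision by at least 20 − x min. That is at least 20 down to 10 min for an assumed LA T2–T3 of 0 to 10 min. The asymmetry rests only on the stated step order and the T2 definition; the size rests also on the assumed x.

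The consequence is confined to one of nine listed secondary outcomes and to what the trial can say about workflow. The primary outcome and the sample size are untouched. A correction is worth making before the data are analysed, because a good measure can be derived from times already collected.

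**What to change.** In the Abstract, Data collection and Secondary outcomes, make entry-to-incision time (T1–T3) the between-group measure of preparation and workflow impact. Keep T1–T2 and T2–T3 as component times reported by arm. Add wording such as: *T1–T2 contains different steps in the two arms (surgical preparation is included in the LA arm and follows T2 in the ESPB arm) and will not be interpreted as a workflow advantage for either arm. T1–T3 in the ESPB arm includes the protocol-mandated minimum interval from block to incision.*

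A test of T1–T2 need not be forbidden. If one is reported, that statement should accompany it, together with the T1–T3 result.

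The cost is small. T1, T2 and T3 are already recorded for all patients, so no data collection, procedure or sample size changes. The trial is ethics-approved and registered (Ethical considerations), so changing a named secondary outcome may need an amendment and a registry update.
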